### Specifics for the Intervention Trial

The core of the study is a pragmatic parallel group, 3-arm nonrandomized multicenter superiority trial with a 1:1:1 allocation ratio (ClinicalTrials.gov NCT05039229).

#### Eligibility and Exclusion Criteria for Individual Participants

All workers employed in, and present at, the processing plants at baseline (T_1_) and follow-up (T_2_) are eligible for answering the self-administered questionnaire. The numbers of invitees for health examinations and individual exposure assessments are limited to a maximum of 99 and 24, respectively, per plant, owing to logistical, financial, and time constraints.

Pregnant participants are excluded from skin prick testing and spirometry, while persons with a history of heart attack or surgical interventions in the eye, stomach, or chest within the preceding 3 months are excluded from carrying out spirometry testing.

#### Intervention Groups and Content of Intervention Follow-Up

##### Overview

While the control group will not receive any intervention, there are 2 different intervention arms that imply measures with the potential to reduce bioaerosol exposure for the employees. These intervention arms represent a general intervention category in which details for the actual intervention are to be developed in collaboration with the factory management and staff. Their involvement ensures local knowledge, including local-specific characteristics, specific location of intervention, other ongoing projects, operation plans, or other aspects that are important to achieve a high effect of intervention measures.

The following sections describe possible alternatives for interventions.

##### Nozzles Intervention

Nozzles intervention (NZ) is a technical intervention targeting alteration of nozzle types, numbers, or nozzle function along the production line, for example, by manipulation of nozzle dimensions, alteration of operating pressure, or shielding of the nozzle’s output stream.

##### Cleaning of Surfaces Intervention

Cleaning of surfaces intervention (CS) is a behavioral or technical intervention related to cleaning of the workers’ personal operating areas (work benches and part of production lines) during work operations or while cleaning floor areas during production hours. This can include increased use of swabbing instead of flushing with water hoses or alterations in use of water hoses for cleaning. Examples for the latter are a reduced flushing frequency, reduction of number of employees executing the work, alterations of hose dimension, or nozzles on hoses.

##### Control Group

For the control group work is to be carried out as usual without any intervention measures.

Interventions in the NZ and CS groups were to be started between 5 and 8 weeks after baseline measurements at time point T_1_. The weeks between T_1_ and T_2_ are hereafter called “intervention weeks.” All 3 arms are followed up in the same way between T_1_ and T_2_. This includes regular contact by phone or email and 1 physical meeting in intervention weeks 31-36. This midway meeting has a scheduled agenda addressing evaluation of baseline fieldwork, suggestions and input for follow-up fieldwork, status of potential technical changes in the plant, as well as assessment of adherence and employees’ experiences of the intervention and study participation.

#### Adherence to the Trial Protocol and Concomitant Activities

Regular contact, midway meetings, and postintervention measurements are one way of increasing adherence in the intervention groups. Local staff involvement in the eventual design of the intervention also has the potential to increase adherence, especially when behavioral changes are part of the intervention.

Although it was expressed to the plants’ management that it is desirable to not engage in any other technical or behavioral changes that could affect the study, there are no restrictions regarding concomitant activities during the study period.

#### Recruitment of Processing Plants and Individual Participants

Participating plants were recruited through earlier collaboration and by establishing new contacts based on regional knowledge about existing factories.

Each plant has a designated contact person from their own staff who helps with recruitment of individual participants and organization and logistics related to fieldwork at T_1_ and T_2_; this person keeps in contact throughout the intervention period.

#### Timeline

Participating factories were recruited during time of funding application. A visit at time point 0 (T_0_), 1-3 weeks before baseline measurements at T_1_, was used for detailed mapping of the specific factory’s infrastructure, a walk-through of the facilities, and for recruiting individual participants through information meetings and distribution of information material. Allocation of intervention groups was done based on this mapping and communicated to the factories in a meeting with company, employee, and safety representatives during the week of baseline measurements at T_1_. The companies then had time to discuss details of the intervention activities internally until the expected implementation period (intervention weeks 5-8).

Individual participants are enrolled with individual consent forms for both health examinations and questionnaires. T_1_ and T_2_ measurements were scheduled within 1 working week (Monday through Thursday). The interval between T_1_ and T_2_ is set to be 12 months (plus or minus 2 weeks).

Table S1 in Multimedia Appendix 2 gives an overview of the timeline of the intervention study.

#### Assignment of Intervention

Randomization of intervention arms was not feasible because of different premises of plant infrastructure. The participating plants were therefore allocated to the study arms by the project group, based on meetings and discussion with the local staff and management, and aiming at covering all 3 study arms in each region. Criteria that were taken into account for allocation to a specific arm were prestudy status of awareness and compliance of bioaerosol-reducing behaviors and technical installation, such as use of swabbing; flushing of work areas during work shifts; number, type, and shielding of water nozzles; water pressure; ventilation system; and plans for any alteration of these factors within the study period.

Allocation concealment and blinding was not relevant for obvious reasons.

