### Data Collection and Management

#### Database

Study data are collected and managed using REDCap electronic data capture tools hosted at the University Hospital of North Norway (UNN) [37,38]. REDCap is a secure, web-based software platform designed to support data capture for research studies; it provides (1) an intuitive interface for validated data capture; (2) audit trails for tracking data manipulation and export procedures; (3) automated export procedures for seamless data downloads to common statistical packages; and (4) procedures for data integration and interoperability with external sources. The main questionnaire and the questionnaires on acute symptoms are filled out in a self-administered paper form and consecutively scanned into the REDCap database. Analysis results on occupational exposure, inflammation markers (blood), skin examinations, skin prick tests, and spirometry will be put into the system by import or manual plotting.

We use the automatic quality check inherent in REDCap, including checking that critical variables have been entered, checking that the participant has consented, and performing range checks and inspection of outliers. Visual data checks are performed for 10% of the manually plotted data in order to identify transcription errors (skin prick tests and lung function measures). Exposure measurements, differential counts, CRP, and IgE are visually checked (100%) after transfer to Excel (Microsoft Corp) sheets. Excel sheets are imported into RedCap and 10% are checked after this process. In addition, 10% of the main questionnaires that are scanned and directly imported into REDCap will be visually inspected and adjudicated.

The database is administered at UNN and will comprise all the original data from T_1_ and T_2_, in addition to metadata and syntaxes (statistical coding) for generated variables. Only a limited number of researchers will have access to the data, as well as have permission to do data entries and corrections.

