### Ethics Approval

This research is carried out in compliance with the Helsinki Declaration of 1975 as revised in 2000, and has been approved by the Regional Committee for Medical Research Ethics North Norway (REK Nord No. 175081). Written, informed consent is obtained from each participant before participation. The consent forms emphasize the right to withdraw from the study at any time without explanation, and that the participants may at any time request that their biological material be destroyed. Information about the study was given orally in an information meeting at T_0_ and orally and in written form during fieldwork (T_1_ and T_2_), with the opportunity to ask questions on-site. Personally identifiable data are entered and analyzed in pseudonymized form by replacing the name with a project-specific identification code, ensuring personal confidentiality. Only the principal investigator and co–principal investigator are given access to a code key that is stored electronically with 2-factor authentication on a safe server at UNN. All personal data will be handled in accordance with GDPR.

The project protocol will ensure that findings reported back to the participants will be analytically valid, clinically significant, and actionable [39,40]. Abnormal lung function measurements, positive skin prick tests, and IgE for salmon-related proteins, and white blood cell count substantially outside the normal range, as well as abnormal white blood cell distribution will be reported back to the participants.

There are ethical concerns related to the common use of workers from outside Norway hired from temporary staff recruitment agencies, as workers with occupational health issues discovered in the project may be lost to follow-up. We will try to avoid this by giving appropriate information at a personal level. All data collection and result analyses will be performed or supervised by experienced investigators trained in good ethical research practices. Scientific and popular scientific publishing will follow the ethical standards for coauthorship and publishing.

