#### Analysis of Data

Detailed description of statistical analyses will be found in the respective scientific publications. In general, for parametric data displaying a normal distribution, results will be presented as arithmetic means with SDs. For data showing a skewed distribution, as is commonly found for exposure measurement data, the results will be presented as geometric means with geometric SDs. Categorical data will be presented as percentages. In case of missing variables, omission or imputation will be performed depending on the type of data.

In general, risk estimates for the various outcomes with 95% CIs will be estimated using a regression model being appropriate for the analysis in question. The estimates will be adjusted for covariates identified as potential confounders, effect modifiers, and mediators. Tests are considered statistically significant at a *P* value of .05.

Analyses related to the intervention study will be performed according to intention-to-treat, regardless of protocol adherence. Results will be reported in line with CONSORT (Consolidated Standards of Reporting Trials) guidelines.

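### Blinding is declared not relevant for the whole trial, although laboratory analysts, data checkers and the statistician could be masked at little cost

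*Protocol article*

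**What the plan says.** The section Assignment of Intervention (protocol article) explains that randomisation was not feasible and that plants were "allocated to the study arms by the project group, based on meetings and discussion with the local staff and management". It ends with one sentence on masking: "Allocation concealment and blinding was not relevant for obvious reasons". No role is distinguished.

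The primary outcome, OM 1, is personal exposure to inhalable total protein (Intervention Outcomes), quantified by BCA assay on filters (Analysis of Bioaerosols).

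The Database section describes what happens to the values afterwards:
- The REDCap quality check includes "performing range checks and inspection of outliers".
- "Exposure measurements, differential counts, CRP, and IgE are visually checked (100%) after transfer to Excel", and the sheets are then imported into REDCap with a 10% check.
- "Only a limited number of researchers will have access to the data, as well as have permission to do data entries and corrections".
- REDCap provides audit trails, and the database keeps all original T1 and T2 data together with the code for derived variables.

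Under Ethics Approval, identifiable data are "entered and analyzed in pseudonymized form by replacing the name with a project-specific identification code". Under Analysis of Data, skewed exposure data are to be presented as geometric means, and "In case of missing variables, omission or imputation will be performed depending on the type of data".

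**The concern.** The practical reasons that rule out masking apply to people who can see the nozzles and hoses. They do not apply to someone reading a plate, reviewing a spreadsheet or fitting a model. The sentence is a stated position for the whole trial, not a detail left to another document, and for those roles it is wrong.

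The trial has few other protections. Allocation was by choice, the article reports 8 plants in the three arms, and concomitant changes at the plants are not restricted. Masked handling of the outcome is one of the few safeguards still available. Exposure data are expected to be skewed, so a decision on a handful of high values can move an arm's mean. If whoever decides knows the plant, arm and visit, that decision can depend on them, even without intent. The researchers allowed to correct data may overlap with the project group that chose the arms; nothing in the article separates the two.

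**Working it through.** **1. Who is masked.** Reading the sections side by side:

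| Role | Can it be masked? | What the article provides |
|---|---|---|
| Plants, workers, field staff | No | Unmasked |
| Laboratory analysts (filters, sera) | Yes, by sample code | No masking stated |
| Those who check and correct data | Yes, by recoded export | Name replaced by a code; plant, arm and visit not said to be hidden |
| Statistician | Partly, by dummy arm codes | No masking stated |

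**2. The plan's own figures.** Sample Size and Power Analysis gives mean 10.0, SD 5.8, alpha .05 and power 80%, with 34, 59 and 133 measurements per group for reductions of 40%, 30% and 20%. With n = 2 × SD² × (1.960 + 0.842)² / difference²:
- difference 4: 33.004, rounded up to 34
- difference 3: 58.7, rounded up to 59
- difference 2: 132.02, rounded up to 133

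All three reproduce (two-sided). Masking does not change them. They supply the yardstick: the smallest planned effect is 20%.

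**3. How skewed.** The article states no geometric SD (GSD). For a log-normal variable with mean 10.0 and SD 5.8, s² = ln(1 + 0.58²) = 0.290, so s = 0.5385 and GSD = 1.71. The geometric mean of 2.7 taken with the arithmetic mean of 10.0 implies s = √(2 ln(10/2.7)) = 1.618, so GSD = 5.04. The two do not agree. I therefore assume GSD 2.0 to 3.0, which lies between them, and show 1.71 as well.

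**4. Leaving out the top 2% in one arm only** (about 3 of the 144 planned per arm and visit). The cut-off is z = 2.054.
- Fall in arithmetic mean: 1 − Φ(2.054 − s)/0.98
- Fall in geometric mean: 1 − exp(−s × φ(2.054)/0.98) = 1 − exp(−0.0494 s)

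| GSD | s | Arithmetic fall | Geometric fall |
|---|---|---|---|
| 1.71 | 0.5385 | 4.6% | 2.6% |
| 2.0 | 0.7 | 6.9% | 3.4% |
| 2.7 | 1.0 | 12.9% | 4.8% |
| 3.0 | 1.1 | 15.3% | 5.3% |

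A simulation dropping exactly 3 of 144 gives 4.5% and 2.6% at GSD 1.71. At GSD 5.04 it gives 28.5% and 7.7%.

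**5. Effect on false positives.** I simulated log-normal data with no true effect, 144 per arm, a two-sided t-test at .05, and the highest values dropped from one arm only. Ranges run over GSD 1.71 and 5.04.

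| Values dropped | Log scale | Raw scale |
|---|---|---|
| 0 | 0.048 | 0.037-0.048 |
| 3 | 0.073-0.077 | 0.113-0.171 |
| 5 | 0.106-0.111 | 0.191-0.306 |

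The CS arm has 2 plants. At 144/3 = 48 measurements per plant that is 96, and dropping 5 gives about 0.14 (log) and 0.24-0.27 (raw). The simulation treats measurements as independent and ignores clustering by plant. The number of values dropped is an assumption.

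**The case against.** The strongest reply is that the mechanism is not in the article. A reader might infer that high values will be dropped, and by the people who allocated the arms. Neither is stated. The checks are described as data-quality steps, and the omission or imputation wording concerns missing variables, not outliers. Those with correction rights are only said to be a limited number of researchers; overlap with the project group is possible but not documented. This stands, and the point does not rest on either reading.

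Safeguards exist as well: audit trails, retained original data, stored code and pseudonymisation. They make changes traceable, which narrows the route. They do not stop a decision from being made with the arm in view, and the Excel check precedes import into REDCap.

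A reader might also infer that the shift rivals the 20% effect. On the geometric scale, which the article names for skewed data, it does not: about 3-5% at GSD 2.0 to 3.0. Only on the raw scale with strong skewness does it come close. The raw scale cannot be dismissed, since the power calculation uses arithmetic means and OM 1 speaks of mean concentration. A rule applied alike in all arms would largely cancel. BCA is also a fairly objective assay, so the exposure lies more in checking and analysis than in the laboratory.

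Finally, laboratory codes and lock procedures commonly sit in other documents. Their absence here is not the point; the affirmative statement that blinding is not relevant is.

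**Conclusion.** The blanket sentence is wrong for laboratory, data-checking and analysis roles, and no section masks them. Together with non-random allocation and discretionary checking and correction, this leaves an avoidable route to bias, partly limited by audit trails and retained original data.

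Its size is conditional on three assumptions: log-normal exposure, GSD 2.0 to 3.0, and the top 2% left out in one arm only. It is then about 3-5% on the geometric scale and 7-15% on the arithmetic scale, or about 4.5% arithmetic at GSD 1.7, against 20%. No bias is shown, and there is no evidence of arm-dependent exclusions. The change is worth making because it is cheap and still possible: the article reports follow-up as incomplete and data-quality checking as unfinished.

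**What to change.** Replace the sentence in Assignment of Intervention with:

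> Plants, workers and field staff cannot be blinded. Remaining filters and sera are analysed under codes that do not show plant, arm or visit. Outlier, exclusion, correction and below-detection decisions for OM 1-OM 5 and OM 13 are made and locked on data with plant, arm and visit masked, including a masked review of T1 values already analysed. The OM 1 model and analysis set are fixed before arm codes are revealed.

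The cost is relabelling of samples, a recoded data export and a code list kept apart from the analysts. Sample size, interventions and field procedures do not change. The mask will be imperfect: there are few plants, and the CS arm can be recognised by having only 2. For T1 samples already analysed, only the review of values can be masked, not the assay.

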### Data Collection and Management

#### Database

Study data are collected and managed using REDCap electronic data capture tools hosted at the University Hospital of North Norway (UNN) [37,38]. REDCap is a secure, web-based software platform designed to support data capture for research studies; it provides (1) an intuitive interface for validated data capture; (2) audit trails for tracking data manipulation and export procedures; (3) automated export procedures for seamless data downloads to common statistical packages; and (4) procedures for data integration and interoperability with external sources. The main questionnaire and the questionnaires on acute symptoms are filled out in a self-administered paper form and consecutively scanned into the REDCap database. Analysis results on occupational exposure, inflammation markers (blood), skin examinations, skin prick tests, and spirometry will be put into the system by import or manual plotting.

We use the automatic quality check inherent in REDCap, including checking that critical variables have been entered, checking that the participant has consented, and performing range checks and inspection of outliers. Visual data checks are performed for 10% of the manually plotted data in order to identify transcription errors (skin prick tests and lung function measures). Exposure measurements, differential counts, CRP, and IgE are visually checked (100%) after transfer to Excel (Microsoft Corp) sheets. Excel sheets are imported into RedCap and 10% are checked after this process. In addition, 10% of the main questionnaires that are scanned and directly imported into REDCap will be visually inspected and adjudicated.

The database is administered at UNN and will comprise all the original data from T_1_ and T_2_, in addition to metadata and syntaxes (statistical coding) for generated variables. Only a limited number of researchers will have access to the data, as well as have permission to do data entries and corrections.

#### Biobank

Biological specimens (serum and plasma) are transferred and stored in a pseudonymized form in a project specific biobank at UNN for later analyses.

#### Data Management Group

The project has established a data management group comprising of the principal investigator and leaders of the 6 work packages (WPs). If not covered by the group of WP leaders, each center is represented by up to two other researchers. The data management group will ensure that the publication plan covers the research questions in the protocol, handle applications of data and biomaterial, and make sure that the data management in the project is in compliance with the approvals from the ethical board and General Data Protection Regulation (GDPR). A data management plan further describes data security issues and ethics regarding data management.

#### Ownership and Use of Data

As this project is a multicenter study, an agreement of ownership and use of data has been completed among the 3 study centers. Agreements between the 3 study centers and the participating plants, ensuring mutual commitment to its collaboration, have also been signed. All data will be archived for 10 years after study termination. Extension of data archives beyond 10 years must seek special approval by the Norwegian ethical committees.

#### Data Access

The participant-level data set will not be available for public access owing to the GDPR. Metadata and statistical codes (syntaxes) beyond those reported in publications will be available upon reasonable request.

### Ethics Approval

This research is carried out in compliance with the Helsinki Declaration of 1975 as revised in 2000, and has been approved by the Regional Committee for Medical Research Ethics North Norway (REK Nord No. 175081). Written, informed consent is obtained from each participant before participation. The consent forms emphasize the right to withdraw from the study at any time without explanation, and that the participants may at any time request that their biological material be destroyed. Information about the study was given orally in an information meeting at T_0_ and orally and in written form during fieldwork (T_1_ and T_2_), with the opportunity to ask questions on-site. Personally identifiable data are entered and analyzed in pseudonymized form by replacing the name with a project-specific identification code, ensuring personal confidentiality. Only the principal investigator and co–principal investigator are given access to a code key that is stored electronically with 2-factor authentication on a safe server at UNN. All personal data will be handled in accordance with GDPR.

The project protocol will ensure that findings reported back to the participants will be analytically valid, clinically significant, and actionable [39,40]. Abnormal lung function measurements, positive skin prick tests, and IgE for salmon-related proteins, and white blood cell count substantially outside the normal range, as well as abnormal white blood cell distribution will be reported back to the participants.

There are ethical concerns related to the common use of workers from outside Norway hired from temporary staff recruitment agencies, as workers with occupational health issues discovered in the project may be lost to follow-up. We will try to avoid this by giving appropriate information at a personal level. All data collection and result analyses will be performed or supervised by experienced investigators trained in good ethical research practices. Scientific and popular scientific publishing will follow the ethical standards for coauthorship and publishing.

